## Abstract

**Background:**

There are few high-quality instruments for evaluating the effectiveness of Evidence-Based Practice (EBP) curricula with objective outcomes measures. The Fresno test is an instrument that evaluates most of EBP steps with a high reliability and validity in the English original version. The present study has the aims to translate the Fresno questionnaire into Spanish and its subsequent validation to ensure the equivalence of the Spanish version against the English original.

**Methods and design:**

The questionnaire will be translated with the back translation technique and tested in Primary Care Teaching Units in Catalonia (PCTU). Participants will be: (a) tutors of Family Medicine residents (expert group); (b) Family Medicine residents in their second year of the Family Medicine training program (novice group), and (c) Family Medicine physicians (intermediate group). The questionnaire will be administered before and after an educational intervention. The educational intervention will be an interactive four half-day sessions designed to develop the knowledge and skills required to EBP. Responsiveness statistics used in the analysis will be the effect size, the standardised response mean and Guyatt's method. For internal consistency reliability, two measures will be used: corrected item-total correlations and Cronbach's alpha. Inter-rater reliability will be tested using Kappa coefficient for qualitative items and intra-class correlation coefficient for quantitative items and the overall score. Construct validity, item difficulty, item discrimination and feasibility will be determined.

**Discussion:**

The validation of the Fresno questionnaire into different languages will enable the expansion of the questionnaire, as well as allowing comparison between countries and the evaluation of different teaching models.

## Background

Several systematic reviews have addressed the issue of the effectiveness of educational programs on Evidence Based Practice (EBP) in improving knowledge, skills and behaviour. In summary, these reviews, have consistently reported that EBP training results in improvements in participants' knowledge of methodological and statistical issues and enhances their attitudes towards the use of medical literature in clinical decision making, but no change in behaviour is found. [1-6] Nevertheless, these findings need to be interpreted with considerable caution as most of the studies had poor internal validity. [7] Furthermore, few authors provided detail on how the questionnaires were developed and validated, how the questionnaires were administrated and how long before the intervention.

Another systematic review assessed the available EBP teaching instrument methods.[8] They defined 3 levels of instruments, based on: (a) the type, extent, methods, and results of psychometric testing and (b) suitability for different evaluation purposes. Level 1 instruments are supported by established inter-rater reliability (if applicable), objective (non-self-reported) outcome measures, and multiple (≥ 3) types of established validity evidence (including evidence of discriminative validity). Therefore level 1 instrument are distinguished by the ability to discriminate between different levels of expertise or performance and are suited to document the competence of individual trainees. Furthermore, the robust psychometric properties in general support their use in formative or summative evaluations.

With the exception of the instruments classified as level 1[8], the rest of instruments should be used cautiously by educators to assess the EBP competence of individual trainees because they were developed to evaluate the effectiveness of specific curricula and lack evidence for discriminative validity. Within level 1 instruments the Fresno Test [9] and the Berlin Questionnaire [10] represent the instruments that evaluate most of EBP steps. The other instruments classified as level 1 evaluate a narrower range of EBP steps.

The Fresno questionnaire was designed to assess all domains of EBP.[9] It begins with the presentation of two scenarios that suggest clinical uncertainty. Short answer questions about the clinical scenarios require the candidate to formulate a focused question, identify the most appropriate research design for answering the question, show knowledge of electronic database searching, identify issues important for determining the relevance and validity of a given research article, and discuss the magnitude and importance of research findings. Unlike multiple choice or true-false questions, the open ended questions require examinees to show higher order thinking in response to an authentic task. These questions are scored by using a standardised grading system.

Table 1 shows the psychometric properties of both questionnaires. It can be concluded that both are reliable and valid for detecting the effect of instruction in EBP. More time and expertise are required to grade the Fresno Test. [8] The multiple-choice format of the Berlin Questionnaire restricts assessment to EBP applied knowledge but also makes it more feasible to implement. Nevertheless, there is another important difference between them: whereas the Fresno test was designed to assess all domains of EBP, not all skills in EBP are captured by the Berlin test (i.e., formulation of question, competencies in searching), which is concentrated more on the handling of research information. In taking the Fresno Test, trainees perform realistic EBP tasks, demonstrating applied knowledge and skills. For this reason we have chosen for translation the Fresno test.

**Table 1 T1:** Properties of Berlin and Fresno test

**Test property**	**Measure used**	**Performance of Berlin test **[10]	**Performance of Fresno test **[9]
**Content validity **(test covers entire topic of interest)	Expert opinión	Expert opinion (five teachers in EBP)	Revisions based on experts' suggestions

**Inter-rater reliability **(degree to which 2 scorers rate a single performance similarly)	Inter-rater correlation	Total score 0.96 (IC 95%: 0.92–0.98)	Ranged from 0.76 to 0.98 for individual items, total scores 0.98

**Internal reliability **(degree to which all test questions on the test measure a single construct)	Cronbach's α average of all possible split half correlations	0.75	0.88

**Item difficulty **(relative difficulty of each item)	% of candidates who answer achieve a passing score	Not given	Ranged from moderate (73%) to difficult (24%); no easy items

**Item discrimination **(ability of each item to discriminate between those with overall high scores and those with overall low scores)	Item discrimination index (ranges from -1.0 to 1.0)	Not given	Ranged from 0.41 to 0.86, no items had negative or weak discriminations

**Construct validity **(evidence that the test measures the construct it intends to)	Mean scores of experts and novices compared by *t *test	Significant difference, higher expert scores than novices	Significant difference, higher expert scores than novices

*Adaptation of Ramos et al[9]

The primary aim of the study is the translation of the Fresno questionnaire into Spanish and its subsequent validation to ensure the equivalence of the Spanish version against the English original.

The specific objectives are: (a) To translate the test into Spanish using the back translation method; (b) To assess the construct validity of the test comparing the scores achieved by tutors with formal methodological training in EBP, the scores of a group of family medicine residents before they have had any formal training in EBP, and finally the scores of a group of family medicine residents with intermediate experience (training) in EBP; (c) To assess the responsive validity (change in knowledge and skills) of the test after a short course in EBP carried out in a group of family medicine residents; (d) To assess the reliability of the test by measuring the internal reliability (degree to which all test questions on the test measure a single construct), the inter-rater reliability (degree to which two scorers rate a single performance similarly), the intra-rater reliability (degree to which onescorer rate a single performance similarly); (e) To assess the feasibility of implementation by reporting the time required administering the test and reporting the time required scoring the instrument.

## Methods and design

The study comprises two stages: translation of the instrument into Spanish and its subsequent validation.

### Setting and context

The setting of the study will be the Primary Care Teaching Units in Catalonia (PCTU). At the beginning of the Family Medicine residence program (which longs four years) the medical residents are enrolled into a PCTU. Each PCTU comprises several health centers in a defined geographical area. There are seventeen PCTU in Catalonia.

The number of medical residents in each PCTU ranged from 2 to 52 in 2007. In the year 2007 there were 202 residents in their second year of training.

### Participants and study description

The instrument will be validated by administering it to a three groups: (a) the first group will comprise by tutors of family Medicine residents with formal methodological training in EBP and who participate regularly in randomised clinical trials conducted in primary care (expert group); (b) the second group will be formed by medical residents in their second year of the Family Medicine training programme in Catalonia, before they have had any formal training in EBP during their residence program (novice group); (c) finally, the questionnaire will be administered to a group of Family and Community Medicine physicians (intermediate experience).

In the present study the group of novices, as well as the group of intermediate experience will receive an educational intervention on EBP about four weeks after completing the pre-test. The last day of the course the test will be administered again allowing for the assessment of the responsiveness of the test. Since there are two groups with different experiences it could be expected that the responsiveness would be different, fostering the expansion of the result.

The following variables will be recorded for each participant: age, sex, year of graduation in medicine, courses in EBP completed prior to the educational intervention and time required in filling-in the test.

### The translation into Spanish

First of all, an e-mail letter will be sent to the original developers of the Fresno test asking permission to proceed with the translation and using of the tool for research purposes.

The test will be translated and back-translated according to guidelines for questionnaire adaptation in order to achieve the highest possible content validity [11,12] (Figure 1).

**Figure 1 F1:**
[figure not shown]
**Translation process of the Fresno questionnaire into Spanish**.

The original English version of the Fresno questionnaire will be translated into Spanish independently by two bilingual translators. A team made up of EBP experts, specialists in Family and Community Medicine and specialists in Preventive Medicine and Public Health, will review the translations. Based on the translations and the comments raised by the research team, an agreed version of the questionnaire will be obtained.

The next step will be to translate the agreed English version to make sure that it is conceptually equivalent to the original. Subsequently, the research team, with assistance from all the translators, we will compare the back translation with the original version in order to identify any questions that are not equivalent or which may be problematic.

Once the agreed version will obtained, a series of individual interviews will be conducted with residents and specialists in Family and Community Medicine to assess the understanding of the questionnaire (cognitive debriefing). The aspects that will be evaluated in the interviews are the degree of understanding of the items, the ease or difficulty in filling-in the questionnaire and the degree in which the format will be accepted. The interviews will be conducted with 5 residents and 5 specialists in Family and Community Medicine. The paraphrasing method will be used in the interviews, where the participants rephrase in their own words the items that present the greatest difficulty.

Finally, the research team will meet to evaluate the results of the questionnaire comprehension tests and obtain the final version of the pre-test.

### Educational intervention

The educational intervention that medical residents receive during their training program is an intensive and interactive four half-day session designed to develop the knowledge and skills required to practice evidence-based care. The audience is the residents performing the second year of the residence program. The course is compulsory for the residents in this specialty. Regarding the present study, lecturers will be advised not to modify their sessions with a view to coaching for the test.

The EBP course includes a series of short lectures and small group facilitate workshops design to teach the principles and practice of evidence based medicine. The emphasis is on practical and efficient point-of-care information retrieval, appraisal, and application at the bedside. At the end of the instruction an evaluation is mandatory. Until now the assessment had been a multiple choice questionnaire.

The course is modelled after the steps of EBP first described in 1992 by Cook DJ, et al.[13] Sessions featured a mix of, interactive lectures, workshops and case-based studies around six topics: Writing a clinical question; searching the medical literature; Selecting and obtaining the evidence; Critical appraisal of systematic reviews, randomised clinical trials (RCTs) and diagnostic test; Interpreting the clinical relevance and precision of the results; Application of evidence to clinical care.

### Administration of the test

To allow the assessment of responsiveness the test will be administered before and after the educational intervention. Repeated administration of measures, particularly those focussing on knowledge, may over-estimate the educational effect and therefore the responsiveness of the test. To minimise the recall bias two sets of test with different scenarios will be prepared. Moreover the pre-test will be administered four weeks before starting the educational module.

Novice and intermediate experience participants will be invited four weeks before starting the educational module to attend a conference about research in primary care and the importance of applying the results of this research into clinical practice. The project of validation the Fresno test will be also presented. The sessions will be decentralised by Health Regions. At the end of each session participants will receive the test (before test). The other test will be administered again on the last day of the course (after test).

The members of the expert group belong to a network of physicians who are regularly engaged in the design and conduct of clinical trials. The network holds in November its annual conference. The members who attended the conference will be asked for filing-in the test. In order to assess the equivalence of the two sets of the questionnaire, both sets will be randomly assigned among the folders distributed to the participants.

In order to assess the feasibility of the test the time required for filling-in the test will be recorded in all cases.

All the participants will be explicitly informed about the research character of the test and that participation was voluntary.

### Scoring the test

To score the test the forms will be encoded and the personal identification data removed from all the participants. Two scorers will score independently the test. They will be blind to the identity of the participants, but not if the questionnaire is given before or after the educational intervention. Previously they will perform a pilot test scoring with ten tests to agree with the scoring methodology.

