### Responsiveness

Responsiveness is the extent to which instruments are sensitive enough to detect the smallest difference considered clinically relevant. [14] Responsiveness is a special type of construct validity.

To calculate the responsiveness of a test and to inform it to the readers is of great importance when planning a clinical trial. Indeed, the more responsive an instrument, the smaller is the number of the patients required to achieve statistical power, or alternatively, the more power is achieved with the same sample size.

Responsiveness statistics used in the analysis will the effect size, the standardised response mean, and Guyatt's method.

The effect size is the difference between the mean baseline and follow-up scores on the measure, divided by the standard deviation of the baseline scores. The effect size is defined as "small" (E-S < 0.2), "small to moderate" (E-S between 0.2 and 0.5), "moderate to large" (E-S between 0.51 and 0.79), "large" (E-S > 0.79), as suggested by Cohen.[15] The results were categorized by group of experience (novice and intermediate).

The Standardised Response Mean (SRM) is calculated as the mean change in scores divided by the standard deviation of these changes. Again the results were categorized by group of experience.[16]

The formula for Guyatt's responsiveness index is defined as Δx/√2 × MSEx, where Δx is the minimally clinically important change on the measure and MSEx is the mean squared error of the variable obtained from an analysis of variance model that examines repeated observations of the measure in clinically stable subjects.[17] Alternatively, if there are only two observations of the measure, MSEx is the standard deviation of the individual change scores in clinically stable patients (i.e., placebo-treated patients). In the present study we assume that the most stable participants were those in the expert group. This index is sometimes referred to as the modified standardised response mean, or to as the index of responsiveness.[16]

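### Both scorers of an open-ended test know whether each form comes from before or after the course, which exposes the effect size and SRM to a shared scoring bias that rater agreement cannot show

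*Protocol article*

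**What the plan says.** Under Scoring the test, the Protocol article states that "the forms will be encoded and the personal identification data removed from all the participants", that "Two scorers will score independently the test", and then, of those scorers: "They will be blind to the identity of the participants, but not if the questionnaire is given before or after the educational intervention". The masking therefore covers identity and expressly excludes occasion. No reason is given.

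The same section adds a calibration step: "Previously they will perform a pilot test scoring with ten tests to agree with the scoring methodology". The Background describes the material to be graded: "the open ended questions require examinees to show higher order thinking in response to an authentic task". Its next sentence says "These questions are scored by using a standardised grading system".

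Under Responsiveness, the effect size is the "difference between the mean baseline and follow-up scores on the measure, divided by the standard deviation of the baseline scores", and the standardised response mean (SRM) is the mean change over the SD of the changes. The Discussion acknowledges that the before-after design has no control group.

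**The concern.** The label left visible to the scorers, before or after, is the contrast that the responsiveness analysis estimates. Scorers who expect a course to improve answers may give borderline free-text answers more credit on after-forms, or less on before-forms, without intending to. With no untaught comparison group scored on two occasions, nothing in the design separates such a tendency from a real gain.

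The plan takes this kind of threat seriously elsewhere. Administration of the test warns that repeated testing may inflate the apparent educational effect and hence the responsiveness, and it answers with two scenario sets and a four-week interval. Unmasked scoring could push the same estimate in the same direction, yet it has no safeguard of its own and is missing from the limitations in the Discussion.

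Responsiveness is one of the five specific objectives, and the Discussion notes that the original validation did not assess it. The Responsiveness section also says that such results inform trial sample sizes. An inflated index would lead later users to plan studies that are too small.

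**Working it through.** The article gives no figure on this point to reproduce. The check is algebra on its own definitions, followed by an illustration under stated assumptions.

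**Inputs from the article.** The effect size and SRM definitions; the category cut-offs (below 0.2; 0.2 to 0.5; 0.51 to 0.79; above 0.79); and Guyatt's index, whose numerator is the minimally important change and whose variability is taken from the expert group. All are under Responsiveness.

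**Assumed, because the article gives no value.** Baseline SD of 20, 30 or 40 points; net scorer shift b of 2, 5 or 10 points, constant across forms; pre-post correlation r of 0.3, 0.5 or 0.7; equal SDs before and after.

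**1. Effect size.** With true mean change D, the estimate is (D + b)/SD_before = true effect size + b/SD_before. The amount added is:

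| Shift b | SD 20 | SD 30 | SD 40 |
|---|---|---|---|
| 2 | 2/20 = 0.10 | 2/30 = 0.07 | 2/40 = 0.05 |
| 5 | 5/20 = 0.25 | 5/30 = 0.17 | 5/40 = 0.125 |
| 10 | 10/20 = 0.50 | 10/30 = 0.33 | 10/40 = 0.25 |

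**2. Against the plan's categories.** The two middle bands are 0.50 − 0.20 = 0.30 and 0.79 − 0.51 = 0.28 wide. At SD 30, a 5-point shift takes a true 0.50 to 0.67 (one band up) and 0.70 to 0.87 (into the top band). It takes 0.30 to 0.47, which stays in its band. A 10-point shift turns a true 0 into 0.33.

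**3. SRM.** The amount added is b/SD_change, with SD_change = SD × √(2(1 − r)). At SD 30 and b = 5, this is 0.14 for r = 0.3, 0.17 for r = 0.5 and 0.22 for r = 0.7.

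**4. Guyatt's index.** Under the Responsiveness definition, b enters neither term. The minimally important change is not the observed change, and the variability comes from experts, who do not take the course. The Discussion lists this index next to mean change scores. Only if the observed change were used as the numerator would b enter.

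**5. Would rater agreement show it?** A simulation of 200,000 participants used SD 30, r = 0.5, a true change of 15 points and independent scorer error with SD 5, and gave both scorers the same shift on after-forms:

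| Shared shift | Effect size | SRM | ICC before | ICC after | ICC pooled |
|---|---|---|---|---|---|
| 0 | 0.50 | 0.49 | 0.973 | 0.973 | 0.975 |
| 5 | 0.66 | 0.66 | 0.973 | 0.973 | 0.976 |
| 10 | 0.83 | 0.82 | 0.973 | 0.973 | 0.977 |

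Within an occasion, the ICC stays at 900/(900 + 25) = 0.973 whatever the shift. The planned agreement analysis would look equally good with or without the bias.

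**The case against.** The strongest reply is that scoring is structured. There is a standardised grading system, the scorers calibrate on ten tests and they work independently. Table 1 reports inter-rater correlations for the original test of 0.76 to 0.98 by item and 0.98 for the total. This stands in part: a rubric narrows the room for leniency, so a large shift is less likely than with free grading. But calibration and independence act on differences between scorers, and high agreement is compatible with a tendency that both share.

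A second reply is that the rest of the validation does not depend on the before-after contrast. That is largely right. Translation, internal consistency and feasibility do not rest on it, and construct validity compares expert forms with before-forms only. That comparison would be exposed too if scorers could tell expert forms from before-forms, but the article does not say whether they can.

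Three stronger readings are tempting but not supported:

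- A reader might infer that leniency passes in full into all three responsiveness indices. It enters the effect size and SRM divided by an SD, and it does not enter Guyatt's index as defined.
- A reader might infer that one set is always used before the course and the other after, so that the scenario itself reveals the occasion. Administration of the test says only that the other test is given at the end. It states random assignment for experts and is silent on the order for learners.
- A reader might infer that shared knowledge of occasion inflates the agreement statistics. In the simulation, the within-occasion ICC did not move and the pooled ICC rose by about 0.002.

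**Conclusion.** The concern holds as a risk of bias. The plan states the lack of masking outright, and neither the scoring section nor the limitations justify or offset it. It bears on the mean change, the effect size and the SRM in both taught groups, and the planned agreement statistics cannot detect it.

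Its size cannot be derived from the article. For assumed baseline SDs of 20 to 40 points, a 5-point net shift adds 0.125 to 0.25 to the effect size, which can change the reported category when the true value lies near a cut-off. Nothing in the article shows that a shift of 5 points, or any shift, will occur, so it would be wrong to conclude that the responsiveness results will be inflated by a known amount. What can be said is that, as planned, they could not be defended against that charge.

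**What to change.** Extend the coding already planned. Before scoring starts, give every form a random code that hides occasion and group (expert, intermediate, novice) as well as identity, and remove dates. Shuffle before-, after- and expert forms together, have both scorers grade in that order, and unlock the codes only after scores are final.

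State how the two sets are allocated to novice and intermediate participants. If one set would otherwise always come first, balance the sets across occasions so that the scenario does not reveal timing.

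The cost is modest. Scoring starts only when form collection ends, or when batches that mix both occasions are complete, and an existing team member who is not a scorer must hold the code list. No further participants are needed. Educational intervention says that an end-of-course evaluation is mandatory. If this test is to serve as that evaluation, which the article does not say, residents' results would come later, and mixed batches would shorten the delay.

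If forms have already been graded with the occasion visible, only independent masked rescoring would remove the problem. Failing that, unmasked scoring should be listed among the limitations of the responsiveness results.
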